## Abstract

**Introduction: **The
WHO currently recommends giving pneumococcal conjugate vaccines (PCVs) as three doses – either three doses in infancy with Pentavalent vaccine (3p+0), or two doses in infancy followed by a booster around 12 months (2p+1). However, their high price is a barrier to introduction and sustainability in low and middle-income countries. We hypothesize that a schedule with a single priming and a booster dose (1p+1) may maintain similar levels of protection for the community by sustaining herd immunity, once circulation of vaccine types has been controlled.

**Methods and analysis: **We will conduct a cluster randomized trial with four intervention arms (1p+1, 0p+1, 2p+1, 3p+0) and three unvaccinated clusters in the 27 communes of Nha Trang, central Vietnam. A PCV catch-up vaccination campaign to all children under three years of age will be performed at the start of the trial. The primary endpoint is non-inferiority of the1p+1 schedule if compared to the WHO standard 2p+1 and 3p+0 schedules in reducing vaccine serotype carriage prevalence in infants. We will also explore impact of 0p+1 schedule. A baseline and annual pneumococcal carriage surveys of 6480 participants per survey covering infants, toddlers and their mothers will be conducted.

**Ethics and dissemination:** Ethical approvals were obtained from the ethical review committees of Institute of Tropical Medicine, Nagasaki University (151203149-2) and the Ministry of Health, Vietnam (1915/QD-BYT). The results, interpretation and conclusions will be presented at national and international conferences, and published in peer-reviewed open access journals.

**Trial registration number: **NCT02961231

## Introduction

Before the widespread use of pneumococcal conjugate vaccines (PCVs)
*Streptococcus pneumoniae* was associated with about 14.5 million episodes of serious pneumococcal disease and more than 800,000 deaths globally in children younger than five years
^
1
^, with the highest burden among low and middle income countries
^
2
^. While PCVs have substantially reduced the burden of pneumococcal disease, their high price has delayed PCV introduction among middle income countries without financial aid, and will make it difficult for low income countries that have introduced PCVs with the help of the Gavi, the Vaccine Alliance, to sustain their programs once they transition from Gavi support
^
3
^.

WHO currently recommends giving three PCVs doses – either three doses in infancy (3p+0), or two doses in infancy followed by a booster around the end of the first year of life (2p+1)
^
4
^. The 3p+0 schedule is used in most low-income countries introducing PCV with Gavi support and aims to provide maximum direct protection early in life where young children are most susceptible to pneumococcal disease. However, almost all high-income countries are using a booster dose schedule that in addition aims to prevent transmission and hence to induce herd protection
^
5
^.

PCV programs have been designed to provide optimal individual protection of the vaccinees, yet experience in both high income and low income countries indicates that herd immunity, which is generated by reducing carriage and hence transmission of vaccine serotypes in the community, can control vaccine type pneumococcal disease in vaccinated and unvaccinated individuals alike
^
6
^. Hence it has been proposed that a schedule with a single priming and a booster dose (1p+1) may maintain similar levels of protection for the community by sustaining herd immunity, once circulation of vaccine types has been controlled by the use of higher dose regimens, or by a catch-up campaign
^
7
^.

Since, it has been shown that indeed a booster schedule with only a single priming dose induces non-inferior post-booster immunogenicity if compared to a 2p+1 schedule, providing some evidence that such reduced-dose schedule could sustain herd protection as hypothesised
^
8
^. The UK, who had previously spear-headed the reduction from three to two priming doses
^
9
^, has recently decided to move to a national 1p+1 schedule
^
10–
12
^.

Using PCV impact on vaccine type carriage as a marker of vaccine type disease
^
13
^, within this trial we investigate the feasibility of reducing the number of infant doses in the PCV immunization schedule, to make more efficient use of herd immunity in the protection against pneumococcal disease. Rather than observing differences in direct vaccines effects between schedules, our study is designed to directly observe the population level effectiveness of alternative schedules. In order to apply the study outcome in countries using either 3p+0 or 2p+1, we will include both 3p+0 and 2p+1 schedules as control arms in the study. We will also include an investigative 0p+1 arm to test whether population effectiveness can be achieved without a priming dose.

In summary, the following PCV schedules are investigate in this study; (i) 0p+1 – A single dose of PCV at 12 months of age, (ii) 1p+1 – A two-dose schedule of PCV at two and 12 months of age, (iii) 2p+1 – A three-dose schedule of PCV at two, four and 12 months of age, and (iv) 3p+0 – A three-dose schedule of PCV at two, three and four months of age.

(ClinicalTrials.gov Identifier: NCT02961231)

## Methods

### Hypothesis

The cost of PCV use can be greatly reduced by making use of existing herd immunity to protect children against vaccine-type pneumococci. We will reduce the circulation of vaccine-type pneumococci to low levels using a catch-up campaign, after which we will evaluate the ability of a simplified two-dose regimen and an alternative one-dose regimen to prevent the reestablishing of vaccine-type pneumococci.

### Study aims and objectives

To investigate the innovative use of existing and future PCVs to protect communities, in particular in resource-limited settings at lower cost using fewer doses, we will pursue two primary, four secondary and two exploratory objectives as follows:

**
*Primary objective 1*.** We will evaluate non-inferiority of the 1p+1 schedule compared to a 2p+1 schedule in maintaining control of VT carriage in (a) children aged 4-11 months,
*i.e.* after the age of a completed primary series and before age eligibility of a booster dose (this is the population that is most at risk for pneumococcal disease and is likely to receive less direct protection from a reduced primary series), and (b) children aged 14-24 months,
*i.e.* after the age where a booster dose is given (this is the beginning of the age period when most intense transmission of pneumococci is believed to occur).

**
*Primary objective 2*.** We will evaluate the non-inferiority of the 1p+1 schedule compared to a 3p+0 schedule in maintaining control of VT carriage in (a) children aged 4-11 months and (b) children aged 14-24 months

**
*Secondary objective 1*.** We will evaluate non-inferiority of the 0p+1 schedule compared to a 2p+1 and a 3p+0 schedule respectively in maintaining control of VT carriage in (a) children aged 4-11 months, and (b) children aged 14-24 months.

**
*Secondary objective 2*.** We will evaluate non-inferiority of the 1p+1 and 0p+1 schedules compared to 2p+1 and 3p+0 schedules in maintaining control of VT carriage in children from the study areas presenting to the local hospital with clinical pneumonia as part of a long-standing enhanced pneumonia surveillance in the study area
^
14
^.

**
*Secondary objective 3*.** We will measure the effect of catch-up vaccination in the community on VT carriage four months after the second dose for children eligible for catch-up vaccination.

**
*Secondary objective 4*.** We will develop mathematical models to predict the impact of 1p+1 and 0p+1 schedules against vaccine type carriage and disease in Nha Trang if introduced simultaneously to all clusters following a catch up campaign, and infer the impact of such schedules in other transmission settings.

**
*Exploratory objective 1*.** We will measure the impact of PCV vaccination in the four vaccine schedules on pneumonia incidence and the nasopharyngeal serotype distribution and load among pneumonia patients.

**
*Exploratory objective 2*.** We will measure the impact of PCV, delivered according to the different regimens in this study, on admissions associated with specific respiratory viruses, including influenza and respiratory syncytial virus.

### Study site

The study is conducted in the 27 communes of Nha Trang, central Vietnam which is the capital of Khánh Hòa province. Nha Trang is surrounded by the sea to its East and mountains elsewhere and has about 400,000 inhabitants. Of the 27 communes, eight are classified as rural and 19 as urban. Communes are an administrative unit chosen to be of approximately similar population size and are locally organizing facilities including child-care, schooling and first-line medical care. Nagasaki University has been conducting studies in collaboration with local health authorities in this study site since 2007. PCV10 (Synflorix) has been registered in Vietnam since 2016. However, PCV is yet to be introduced into the national immunization program in Vietnam and private market uptake is minimal.

### Study design

We will conduct a Phase IV cluster randomized trial in the 27 communes of Nha Trang city. The four different PCV schedules (1p+1, 0p+1, 2p+1, and 3p+0) form four corresponding intervention arms completed by an informal, non-randomised control arm without PCV use (
Figure 1). The unit of randomization, the clusters, are Nha Trang’s communes. We chose the three clusters that were to remain unvaccinated and randomly allocated the remaining 24 communes into six clusters per intervention arm.

**Figure 1. f1:**
[figure not shown]
Nha Trang PCV Trial design. The clinical trial design showing the initial catch-up vaccination to all children less than 3 years of age in the PCV intervention arms followed by the randomly designated PCV schedules. The outcome of the study is shown as vaccine type pneumococcal carriage in the community and hospitalized pneumonia cases in the study setting.

### Selection of PCV for the study

At the time of initiation of the study, PCV10 was registered in Vietnam, while this was not yet the case for PCV13. Therefore, PCV10 is used in the study.

### Background information and sample size calculation

Carriage surveys among healthy children in Nha Trang as well as in hospitalized children admitted with acute respiratory infection found similar serotype coverage for both PCV10 and PCV13; approximately 65% in healthy and 70% in children with acute respiratory illness
^
15
^. PCV10+6A type pneumococcal prevalence was 33% in healthy infants and 30% healthy toddlers.

### Cluster and sample size calculation

We assumed that (i) the baseline prevalence of carriage of PCV10 serotypes among infants in Nha Trang is 32.5% and varies between communes from 20% to 45% and (ii) that carriage prevalence is reduced to 5% through the catch-up campaign and kept at the same level through routine vaccination under a 2p+1 or 3p+0 schedule.

Nasopharyngeal samples will be collected before the start of PCV vaccination in the site and at 6, 12, 24, 36, 48 and 60 months thereafter from 60 subjects per age groups (4-11mth old children, 14-24mth old children and their mothers) for each of the 27 clusters; adding up to 6,480 swabs per cross-sectional study and 45,360 in total. We assume that 10% of swabs cannot be obtained or cannot be interpreted in the laboratory. We calculated the number of clusters required to test our non-inferiority hypothesis under a type I error probability of 5% and 80% power.

As detailed in Hayes and Moulton
^
16
^ we calculated that 5.37 clusters are required to detect an increase in VT carriage prevalence among children in the 1p+1 arm compared with the 2p+1 or 3p+0 arms of 5% or more. Hence, six clusters for each intervention arm were included.

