### Approach and data analysis

The comparison of carriage prevalence in the intervention (1p+1 or 0p+1) clusters and the gold standard (2p+1 or 3p+0) clusters respectively will allow age-group specific assessment of non-inferiority of the 1p+1 and 0p+1 schedules if compared with the 2p+1 or 3p+0 schedules respectively in regard to protection against vaccine type carriage. The data will be analysed single-blindedly through an intention-to-treat analysis as this yields the most conservative effect that could be observed in a real-world setting. An absolute difference in prevalence of <5% will be used as the non-inferiority margin (see sample size calculations). As the primary analysis we will use a Chi-squared test of a difference in two proportions to estimate the treatment effect (
*i.e.* the difference between 1p+1 and 2p+1 arm VT prevalence in infants) following the approach detailed in Hayes and Moulton
^
16
^ for trials with fewer than 15 clusters per arm. The upper limit of the two-sided 95% confidence interval of the treatment effect not exceeding the specified non-inferiority margin of 5% will indicate non-inferiority.

**

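### The 5.37-cluster requirement assumes a one-sided 5% test and no swab loss; under the protocol's two-sided 95% rule, six clusters per arm give about 71–72% power, not 80%.

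*Protocol article*

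**What the plan says.** In the protocol article, *Cluster and sample size calculation* sizes the trial "under a type I error probability of 5% and 80% power" and does not say whether the 5% is one- or two-sided. It assumes that "carriage prevalence is reduced to 5% through the catch-up campaign" and stays there under 2p+1 or 3p+0. It takes a baseline prevalence of 32.5%, ranging from 20% to 45% between communes, and 60 subjects per age group and cluster. On losses it says: "We assume that 10% of swabs cannot be obtained or cannot be interpreted in the laboratory". Citing Hayes and Moulton, it then reports: "we calculated that 5.37 clusters are required to detect an increase in VT carriage prevalence among children in the 1p+1 arm". Six clusters per intervention arm follow from rounding up.

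*Approach and data analysis* sets the margin ("An absolute difference in prevalence of <5% will be used as the non-inferiority margin") and the decision rule: "The upper limit of the two-sided 95% confidence interval of the treatment effect not exceeding the specified non-inferiority margin of 5% will indicate non-inferiority".

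**The concern.** A non-inferiority conclusion drawn from the upper limit of a two-sided 95% interval has a one-sided error rate of 2.5%. If the cluster count was derived at one-sided 5%, the 80% power belongs to a more lenient test than the one that will be run. The 10% swab loss is stated next to the calculation, so the result should reflect 54 evaluable swabs per cluster and age group rather than 60.

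This affects the primary comparisons: 1p+1 against 2p+1 and against 3p+0, each in two age groups. The article's list of limitations admits limited power only for secondary outcomes, so a reader will take the primary comparisons to have 80%. A failure to show non-inferiority could then be read as evidence against 1p+1 when it may partly reflect a lower chance of success than stated.

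**Working it through.** **Inputs**

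- Prevalence under the control schedules: 5%, taken as equal in the 1p+1 arm (*Cluster and sample size calculation*).
- Margin: d = 0.05 (*Approach and data analysis*).
- Swabs per cluster and age group: m = 60 before losses; 60 × 0.9 = 54 after the stated 10% loss.
- Power: 80%, so z = 0.842.
- Error rate: one-sided 5% (z = 1.645), or one-sided 2.5% (z = 1.960) as the two-sided 95% interval implies.
- Between-cluster coefficient of variation k: the article gives only the range of 20% to 45% around 32.5%. *Assumption:* the range spans four SDs, so SD = 0.25/4 = 0.0625 and k = 0.0625/0.325 = 0.1923.

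**Formula** (unmatched clusters, equal prevalence p = 0.05 in both arms)

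c = 1 + (z_α + z_β)² × V/d², where V = 2p(1−p)/m + 2k²p².

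**Reproducing the article's figure** (one-sided 5%, m = 60)

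- V = 0.095/60 + 2 × 0.1923² × 0.0025 = 0.001583 + 0.000185 = 0.001768
- V/d² = 0.001768/0.0025 = 0.7073
- (1.645 + 0.842)² = 6.183
- c = 1 + 6.183 × 0.7073 = **5.373**, which matches 5.37.

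**Applying the article's own rule and loss** (one-sided 2.5%, m = 54)

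- V = 0.095/54 + 0.000185 = 0.001944; V/d² = 0.7777
- (1.960 + 0.842)² = 7.849
- c = 1 + 7.849 × 0.7777 = **7.10**

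**Power with six clusters**

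- Same formula: Φ(√((6−1)/0.7777) − 1.960) = Φ(0.576) = **71.8%**.
- Noncentral t, 10 df: SE = √(0.001944/6) = 0.0180; noncentrality = 0.05/0.0180 = 2.78; critical value 2.228; power **70.7%**.

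**Each departure separately** (k = 0.1923)

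| Error rate | m | Clusters needed | Power at six clusters (formula) |
|---|---|---|---|
| One-sided 5% | 60 | 5.37 | 84.5% |
| One-sided 5% | 54 | 5.81 | 81.3% |
| One-sided 2.5% | 60 | 6.55 | 75.8% |
| One-sided 2.5% | 54 | 7.10 | 71.8% |

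Under the last row, seven clusters give about 79%, so reaching 80% would take eight.

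**Dependence on k** (one-sided 2.5%, m = 54, six clusters)

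- No between-commune variation (k = 0): 6.52 clusters needed, power 76.0% (74.9% by noncentral t).
- Other readings of the 20% to 45% range, by the formula: SD = range/6 gives 74.1%, range/3.92 gives 71.6%, range/2 gives 60.9%.
- If the CV at 5% prevalence exceeds the value carried over from 32.5% (assumed range, noncentral t): 65% at k = 0.3, 59% at 0.4, 52% at 0.5.

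**Could 5.37 be a two-sided calculation?** With z = 1.960 and m = 60, the formula gives 5.97 even at k = 0, so it cannot return 5.37 for any k.

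**The case against.** The strongest reply is that 5.37 is not miscalculated. A 5% type I error for a non-inferiority hypothesis can be read as one-sided, and on that reading six clusters exceed 80%, even after swab loss (81.3%). This is correct as far as it goes. The fault lies between the two sections, and the loss matters only once the error rate is aligned with the decision rule. But the test that will be run is the two-sided 95% one, and the 80% claim does not carry over to it.

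Second, the SD is inferred: the article does not say what its range represents. Some other input combinations also land near 5.37. One gives 5.366, but it needs the matched-design term and pooling of both age groups, which conflicts with the unmatched allocation and the separate age-group objectives. The exact match makes range/4 the best reading, yet it remains an assumption, and the precise power depends on it. The shortfall itself does not, since power is 76% with no between-commune variation at all.

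Third, without the formula's additional cluster, six clusters give 79.3%. But 5.37 is reproduced only with that term included, and the noncentral t result, which does not use it, is 70.7%.

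Finally, the rule in force is the stricter one, so this mismatch does not raise the risk of a false non-inferiority claim. That is right. The harm is confined to overstated power and to how a failed test would be read.

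**Conclusion.** The concern holds. The article's cluster requirement was derived for a one-sided 5% test with complete swabs. Under its own decision rule and loss assumption, 7.10 clusters per arm are needed, and the six used give about 71–72% power per comparison instead of 80%.

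This rests on 5% prevalence in both arms, the unmatched formula that reproduces 5.37, and SD = range/4. Without the SD assumption, power is at most about 76%, and it is lower if communes vary more, relative to the mean, at 5% prevalence than at 32.5%. Sidedness is the main cause: alone it brings power to 75.8%, and swab loss takes it to 71.8%.

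**What to change.** In *Cluster and sample size calculation*:

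- State the error rate as one-sided 2.5%, matching the two-sided 95% interval, and the evaluable cluster size as 54.
- Give the requirement under those inputs as 7.1 clusters per arm. If 5.37 is kept as a record of the design basis, list the inputs that produce it: one-sided 5%, 60 swabs, and the SD or CV used.
- State that six clusters per arm give about 71–72% power per comparison, and show power over a CV range of 0.2 to 0.5, labelled as an assumption.
- Delete the claim that six clusters meet 80% power.

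Keep the two-sided 95% confidence interval rule; loosening it to rescue the power statement would weaken control of the type I error.

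The cost is wording and a less favourable power statement. No clusters, participants or analyses change.

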### Rationale for inclusion of a single-dose arm

The primary goal of this study is to compare the effect of PCV in a 1p+1 schedule compared to 2p+1 and 3p+0 schedules respectively. However, by extension of the concept of sustaining herd immunity with fewer doses at infancy, a single dose schedule may suffice if the lack of a priming dose does not impair the efficacy of the dose given at 12 months of age. Single PCV doses have been used successfully in toddlers and older children as part of catch-up campaigns to accelerate control of VTs
^
17
^ but haven’t been investigated as a programmatic choice for routine use yet. This trial set-up posed a unique opportunity to include an additional arm that investigates the effectiveness of a 0p+1 schedule in sustaining population protection against VT carriage.

### Selection of communes for the unvaccinated study arm

The three northernmost communes, Vinh Luong, Vinh Phuong, and Vinh Hoa have been assigned to the unvaccinated control arm based on the geographical background,
*i.e.* being somewhat separated from the other Nha Trang communes. Vinh Luong and Vinh Phuong communes are classified as rural communes and Vinh Hoa as an urban commune. Although we will not formally consider these communes as controls for the study as they have not been part of the randomisation, inclusion of unvaccinated communes will provide information on potential year-by-year carriage variations due to introduction of new strains from outside of Nha Trang or from vaccinated communes in Nha Trang.

### Selection of communes for the intervention arms

The remaining 24 communes have been randomized into the four treatment arms. To ensure random but balanced allocation of clusters that were similarly representative of rural and urban communities and that are included in the ongoing hospital-based surveillance, we used automated rejection sampling.

We defined the following set of acceptance criteria:

i)In each arm at least one of the six rural communes must be selected.ii)In each arm at least three of the 16 communes included in the ongoing pediatric hospital-based surveillance for acute respiratory illnesses must be selectediii)No two adjacent clusters can be assigned to the same study arm

The four color theorem
^
18
^ indicates that there is at least one possible sampling permutation that fulfills criteria iii). Using the statistical software R
^
19
^ we developed an algorithm to randomly assign arms to clusters and reject a sample if it violated any of the acceptance criteria above. The program was run until the first sample fulfilled all criteria. In total, 2,793,298 samples were rejected. The final allocation is shown in
Figure 2. The rural-urban distribution and current pneumonia surveillance cluster distribution are shown in
Table 1.

**Figure 2. f2:**
[figure not shown]
PCV schedule cluster allocation of communes in Nha Trang for each arm. Figure of the 27 communes of Nha Trang city. Cluster/communes receiving different PCV schedules are shown in different colours. Name of the communes are also shown in the figure.

**Table 1. T1:** PCV schedule, rural-urban and current pneumonia surveillance cluster allocation.

PCV Schedule	0p+1	1p+1	2p+1	3p+0	Unvaccinated
**Setting**					
**Rural**	1	2	2	1	2
**Urban**	5	4	4	5	1
**Pneumonia surveillance**					
**Yes**	3	3	4	3	3
**No**	3	3	2	3	0
**Total**	6	6	6	6	3

### Initial catch-up vaccination

A catch-up vaccination campaign was done in February 2017 before the start of PCV vaccine introduction in all but the unvaccinated three communes. Three doses of PCV10 have been offered to all children between two and six months of age with an interval of two months between the first and second, and seven months between the second and the third doses. A catch-up of two doses of PCV10 has been offered to children between seven and 18 months of age with an interval of two months between the two doses. Children between 19 and 36 months of age have been offered a single dose. This was expected to quickly control circulation of vaccine serotypes. Children with known allergy to PCV10 will be excluded from the vaccination campaign.

